## **5-5. Treatment Discontinuation Provisions**

**5-5-1. Treatment discontinuation criteria**

If applicable, the attending physician will discontinue subsequent treatments and take appropriate measures. Investigators should observe and inspect for the evaluation items specified in “Table 6 Examination items and evaluation schedule” below at the time of discontinuation and record their findings and the accompanying rationale in their case report. In cases of termination, the attending physician shall promptly submit an administration progress survey to the study secretariat via fax.

1) When a subject him/herself withdraws consent

2) When a subject him/herself requests discontinuation of the protocol treatment

3) When recurrence of the original disease is observed

4) When novel cancerous lesions (duplicated cancer or multifocal colorectal cancer [excluding M cancer]) occurs

5) When the attending physician determines that protocol continuation will be difficult due to deterioration of comorbidities or onset of complications

6) When there is no relief or disappearance of symptoms following withdrawal due to an adverse event that falls under the off-period/dose reduction provisions (delay of treatment start by over 3 weeks or withdrawal)

7) If administration cannot be continued due to the occurrence of an adverse event even after 1 or 2 level reductions under the off-period/dose reduction provisions

8) If an adverse event of Grade IV occurs, the protocol treatment must be discontinued. (If capecitabine treatment is restarted at the discretion of the attending physician after protocol termination, a case report must be submitted.)

9) When the attending physician determines that protocol continuation will be difficult owing to an adverse event

10) If a subject dies

11) When the protocol treatment cannot be continued because the subject was transferred to a hospital

12) If a subject is determined to be ineligible after enrollment

13) Other cases in which the attending physician deems it necessary to terminate the protocol treatment

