# **3. Selection Criteria**

## **3-1. Inclusion Criteria**

1) Patients histologically diagnosed with colon cancer (adenocarcinoma)

2) Cases of histological Stage III* colorectal cancer or sigmoid rectal cancer

*as defined in the Treatment Guidelines for Colorectal Cancer (7th edition)

3) Colorectal cancer cases in which resective surgery was performed (including cases involving D2 or higher lymph node dissection)

4) Cases in which surgery was determined to have achieved cure degree A (Cur A)

5) Patients aged (at time of enrollment) between 20 and 80 years

6) Performacne Status (PS) (Eastern Cooperative Oncology Group [ECOG]): 0 or 1

7) Eligible patients who have not yet undergone chemotherapy or radiotherapy

8) Patients capable of taking meals

9) Patients maintaining stable vital organ functions

a) WBC count ≥ 3,000/mm3 and <12,000/mm3

b) Hemoglobin ≥ 9.0 g/dL

c) Thrombocyte count ≥ 90,000/mm3

d) Serum creatinine ≤ 1.5x hospital standard upper limit

e) Total serum bilirubin ≤ 1.5x hospital standard upper limit

f) AST, ALT ≤ 2.5x hospital standard upper limit

g) ALP ≤ 2.5x hospital standard upper limit

10) Creatinine clearance* >50 mL/min

*: Determined based on the following simple formula to calculate creatinine clearance

Men: [(140-age)×body weight (kg)]/[72×serum creatinine value (mg/dL)]

Women: [(140-age)×body weight (kg)×0.85]/[72×serum creatinine value (mg/dL)]

11) Cases in which the protocol treatment was initiated within 8 weeks after surgery

12) Patients who consented to study participation in writing

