## **4-2. Subject Enrollment**

This study utilized centralized subject enrollment.

1) Register so that treatment can be started within 8 weeks after the date of surgery after confirmation of eligibility under “3. Selection Criteria”. (Note: enroll after confirmation of pathological test results)

2) After obtaining patient consent to study participation, fill out the "case registration form" (Form 1-1) and send to the secretariat via fax.

3) After receiving the case registration form via fax, the secretariat confirms that the prospective subject meets the selection criteria, then calls the study site supervisor as soon as possible. Subject group assignment then occurs, and dosing based on the subject total body surface area is communicated to the site by the secretariat, completing subject “enrollment”. The study secretariat then promptly sends the case registration confirmation form (Form 1-2) to the study site. Each site retains the case registration confirmation form on site and manages subject identification by creating a subject registry, etc.

4) The protocol treatment is initiated within 14 days after enrollment.

* “As soon as possible” means for subject enrollment (9:00-17:00) during business hours (Monday-Friday, excluding public holidays and the Year-End holiday period [December 29-January 4]), within “30 minutes” when submitted via paper during business hours (9:00-17:00) or between 9:00-9:30 the following business day if submitted outside of business hours (e.g., 9:00-9:30 on the next working day).

Japanese Foundation for Multidisciplinary Treatment of Cancer

[name]

[contact] (data center)

[name] (study representative/administration)

[name] (toll-free)

[contact]

E-mail: [contact] (data center)

Hours: Monday-Friday, 9:00-17:00 (excluding weekends, national holidays, and the New Year period (12/29–1/4))

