**5. Treatment Procedures**

## **5-1. Protocol Treatment**

The protocol treatment assigned to each subject starts within 8 weeks after surgery. Subjects’ height and body weight at enrollment are used to calculate dosage, and no dose correction due to changes in body weight is performed.

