## **5-8. Post-treatment**

Post-treatment should not be performed to address underlying illnesses (chemotherapy, endocrine therapy, molecularly targeted therapy, immunotherapy, etc.) until cancerous recurrence is confirmed after termination of the protocol treatment. Post-treatments administered after completion or termination of the protocol treatment and after confirmation of recurrence are not specified.

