# **8. Statistical Matters (Research Evaluation Criteria and Analyses)**

## **8-1. Definition of the Target Population for Analysis**

1) All enrolled subjects: The group of all enrolled subjects excluding duplicate or invalid enrollments.

2) All eligible subjects: The group of all enrolled subjects excluding “ineligible subjects”. However, ineligible subjects are defined as subjects determined to not meet the selection criteria after enrollment, or cases in which it becomes clear that the subject meets 1 or more of the exclusion criteria.

3) All treated subjects: The group of all enrolled, qualified subjects excluding those for whom the protocol treatment was not completed.

Based on the above definitions, the main subject groups targeted for the analysis of efficacy and safety shall be all enrolled subjects and all treated subjects.

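### Section 5-8 advises against chemotherapy before recurrence with no exception for subjects stopped as ineligible, so some Stage III patients are steered away from finishing the 6-month standard

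*Protocol*

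**What the plan says.** Protocol 5-5-1 tells the attending physician to discontinue treatment when a listed criterion applies. Item 12 reads "12) If a subject is determined to be ineligible after enrollment". It does not separate safety grounds from other grounds.

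The only definition of ineligibility is in 8-1, where "ineligible subjects are defined as subjects determined to not meet the selection criteria after enrollment"; meeting an exclusion criterion also counts. One of the selection criteria (3-1, item 11) is "Cases in which the protocol treatment was initiated within 8 weeks after surgery".

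Section 5-8 covers what follows termination: "Post-treatment should not be performed to address underlying illnesses (chemotherapy, endocrine therapy, molecularly targeted therapy, immunotherapy, etc.) until cancerous recurrence is confirmed". Treatment is left open only once recurrence has been confirmed. Nothing in 5-8 depends on why protocol treatment ended.

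The one place that foresees capecitabine being resumed after termination is a parenthesis in 5-5-1 item 8, the Grade IV adverse event item: "If capecitabine treatment is restarted at the discretion of the attending physician after protocol termination, a case report must be submitted".

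Section 2-2-3 concludes that 6 months is the standard adjuvant period, and 5-3-1 sets this at 8 three-week courses for Group A.

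**The concern.** Stopping the trial regimen when a subject proves ineligible is normal and is not disputed. The difficulty is the combination with 5-8. That rule has a clear purpose for subjects who complete treatment or stop for toxicity: it keeps other therapy out of the period before a DFS event. Applied to a subject who tolerates the drug and is ineligible on a technical ground, it points the physician towards observation alone in a disease for which 2-1-2 describes adjuvant chemotherapy as needed. Such a patient could end up with less treatment than the control arm, and less than the same protocol names as standard, for a reason unrelated to tolerability, safety or indication.

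**Working it through.** The plan gives no figure to reproduce. The check is a reading of the sections together, plus simple course counts.

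**1. Does item 12 reach non-safety grounds?** Item 12 is unqualified. Under 8-1 any unmet selection criterion makes a subject ineligible. Criterion 11 (start within 8 weeks of surgery) is a timing rule, not a statement about tolerance of capecitabine.

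**2. Can such a ground come to light after enrollment?** For criterion 11 it must, because enrollment comes before the first dose.
- 4-2 item 1: "Register so that treatment can be started within 8 weeks after the date of surgery".
- 4-2 item 4: "The protocol treatment is initiated within 14 days after enrollment".
- 5-1: "The protocol treatment assigned to each subject starts within 8 weeks after surgery".

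Eight weeks is 8 × 7 = 56 days, and 56 − 14 = 42. A subject enrolled after day 42 can therefore start inside the 14-day limit and still miss day 56. A late start breaches 4-2 item 1 and 5-1, but once it has happened the patient is on drug and fails criterion 11.

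**3. What does the protocol then direct?** 5-5-1 stops capecitabine, and 5-8 advises against chemotherapy until recurrence. Neither section excepts item 12. The restart parenthesis belongs to item 8.

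**4. What is lost against the protocol's own standard?** The standard is 8 courses × 3 weeks = 24 weeks. With k courses received, the share received is k/8 and the weeks lost are 3 × (8 − k).

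| Courses received (k) | Share of standard | Weeks of schedule lost |
| --- | --- | --- |
| 1 | 12.5% | 21 |
| 2 | 25% | 18 |
| 4 | 50% | 12 |
| 7 | 87.5% | 3 |
| 8 or more | 100% | 0 |

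This holds in both arms. A Group B subject stopped during courses 9 to 16 has already had the standard.

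**5. How many patients?** The protocol gives no ineligibility rate. For scale only, each assumed 1% of the 1,200 planned subjects is 0.01 × 1,200 = 12, before removing those who have finished course 8 and those for whom capecitabine is unsafe or not indicated.

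**The case against.** The strongest reply is that the text is flexible. 5-5-1 also tells the physician to take suitable steps, 5-8 is worded as advice, and 11-4 limits adherence where it would unduly endanger patients' safety or rights. The item 8 parenthesis accepts a restart before recurrence even after a Grade IV event, so 5-8 can hardly be an absolute bar. All of this stands, and a reader who inferred that the protocol forbids these patients further capecitabine would go too far. But none of these provisions names the item 12 subject, and only 5-8 speaks directly to chemotherapy after termination.

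The secretariat also confirms the selection criteria before assignment, and enrollment follows the pathology result (4-2). Most ineligibility should surface before dosing. That reduces the reach, but it cannot settle criterion 11, which depends on a first dose not yet given. It is fair to add that a late start needs a prior site error, and that the 8-1 definition is written for an analysis set rather than for clinical use. Item 12 has no definition of its own, so 8-1 is the natural one to apply.

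Two further inferences should be resisted. A reader might take node dissection below D2 as a second trigger, but criterion 3 mentions D2 only in an inclusive parenthesis and does not plainly require it. A reader might also infer from the twice-yearly eligibility monitoring in section 14 that most cases would be found before course 8. The protocol does not state when forms arrive or when ineligibility would be detected, so no such share can be supported.

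Finally, 5-8 applies equally to other non-toxicity stops, such as hospital transfer (item 11). That is true, but it does not remove the gap for item 12.

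**Conclusion.** The point holds as a cheap improvement. Item 12 and 5-8, followed as written, steer a Stage III patient who tolerates capecitabine away from completing the 6-month standard when a non-safety ineligibility is found before the end of course 8. The per-patient shortfall runs from 21 weeks (after course 1) to 3 weeks (after course 7) of a 24-week schedule. The number of patients is unknown and probably very small.

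A reader might infer that the primary comparison is compromised. The documents do not support that: the rule is the same in both arms, ineligible subjects remain in the all-enrolled set used for DFS (8-1, 8-2), and outcome observation continues after treatment stops (5-5-2). The effect there is minor, and no loss of power is claimed.

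The conclusion assumes that item 12 uses the 8-1 meaning of ineligibility, and that a start after 8 weeks does not by itself make capecitabine unsafe or not indicated. The second assumption is a clinical judgement, which the fix leaves to the physician.

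**What to change.** Add one sentence to 5-8: *Subjects stopped under 5-5-1 item 12 may, at the attending physician's discretion, complete capecitabine up to 8 courses in total unless the ineligibility makes it unsafe or not indicated.* Extend the item 8 reporting provision to item 12, and keep these subjects in all-enrolled follow-up as 5-5-2 already provides.

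The permission should name capecitabine and the 8-course limit rather than standard adjuvant therapy in general. Table 1 in 2-2-2 includes oxaliplatin regimens, and 2-2-1 reports that oxaliplatin improved DFS. Broader wording would let a different active treatment in before a DFS event, in subjects who stay in the primary analysis set. Capecitabine up to 8 courses is treatment that both arms were assigned anyway.

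Item 12 stays as it is, so no ineligible Group B subject goes on to courses 9 to 16 under this change. Design, sample size and endpoint are unaffected. The cost is one sentence, one cross-reference, and the recording of a few off-protocol capecitabine courses given before a DFS event.

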**5-5-2. Procedures when the protocol treatment is suspended**

In cases in which the treatment protocol is suspended or cases of the presence of novel cancerous lesions or recurrence 5 years after the last subject enrollment registration is detected, outcome observation is continued, with the exception of cases meeting the following criteria:

1) When a subject withdraws consent to follow-up after withdrawal from the study

2) If a subject dies

3) When tracking a subject is difficult for other reasons

## **5-6. Safety Concerns**

Capecitabine is expected to be administered on an outpatient basis, and safety issues can rapidly become severe if adverse events such as diarrhea occur. If the attending physician observes an adverse event before a subject’s scheduled visit, the attending physician should immediately contact the hospital and instruct the hospital to provide treatment.

Many adverse events associated with capecitabine are reversible and the treatment protocol need not be discontinued, but an off-drug period or dose reduction may be required.

**1) Diarrhea**

Capecitabine has been reported to occasionally cause severe diarrhea. If severe diarrhea occurs, symptomatic treatments such as electrolyte rebalance by infusion may be necessary. If nonsevere diarrhea occurs, administration of common anti-diarrheal agents such as loperamide is effective.

**2) Nephropathy**

The incidence of Grade III/IV adverse events has been found to be higher in subjects with moderate renal dysfunction (creatinine clearance: 30–50 mL/min) compared to those with normal renal function. In this study, subjects with moderate to severe renal dysfunction (creatinine clearance ≤ 50 mL/min) before treatment initiation will be disqualified.

Dose adjustment is unnecessary in subjects with mild renal impairment (creatinine clearance 51–80 mL/min).

**3) Cardiotoxicity**

Myocardial infarction, myocardial ischemia, angina pectoris, arrhythmia, cardiac arrest, heart failure, sudden death, electrocardiogram abnormality, and cardiomyopathy have been observed in patients receiving capecitabine only. These findings are similar to cardiotoxic events reported overseas to be associated with fluoropyrimidine drugs. Care must be taken when administering capecitabine to patients with a history of cardiovascular disease.

**4) Motor Impairment Syndrome**

The severity of hand-foot syndrome is classified from Grade I-III (Table 5). In cases of Grade II/III hand-foot syndrome, “Table 3 Off-period/dose reduction criteria” should be followed.

## **5-7. Concomitant Treatments**

**5-7-1. Contraindicated drugs and therapies**

Do not concomitantly administer other anticancer drugs, immunotherapies, endocrine therapies, unapproved drugs, drugs considered to affect the evaluation of radiation therapies, or experimental drugs.

**5-7-2. Drugs subject to concomitant usage warnings**

1) Oral coumarin anticoagulants

In patients receiving capecitabine and oral coumarin anticoagulants concomitantly, observe coagulation parameters (prothrombin time) frequently to appropriately adjust the anticoagulant dosage. In clinical pharmacology studies, clinically important drug interactions have been observed with respect to concomitantly administered capecitabine and warfarin. Patients taking capecitabine in combination with coumarin anticoagulants such as warfarin and phenprocoumon were reported to exhibit fluctuations in coagulation parameters and bleeding, and cases of patient death have also been reported. Examples have been reported in postmarketing data of cases in which clinically significant prothrombin time prolongation and international normalized ratio (INR) elevation occurred when patients who were stable using anticoagulant began taking capecitabine. These symptoms manifest several months after the initiation of capecitabine administration, and in several cases they also occur within 1 month after discontinuation of administration. Furthermore, these events are not affected by liver metastasis. Patient age of over 60 years and onset of cancer are both risk factors for the development of coagulopathy. Use of low molecular weight heparin instead of coumarin is safe under the guidance of a physician.

2) Phenytoin

Increase in plasma phenytoin concentration has been reported as a result of concomitant use of the antiepileptic drug phenytoin and oral capecitabine. Accordingly, when capecitabine and phenytoin are used in combination, plasma phenytoin concentration should be observed periodically, and patients should be monitored for subjective symptoms, and changes in clinical laboratory values.

**5-7-3. Safe drugs for concomitant use and recommended supporting treatments**

Drugs other than those specified in “Contraindicated drugs and therapies” may be used concomitantly based on the judgment of the attending physician. For concomitant medications and concomitant treatments (including treatment, etc.), describe the name of the medicine (treatment), the period of the combination use, and the reason for the combination in the case report.

1) Supportive care for hand-foot syndrome

There is currently no established treatment method, but as symptomatic treatment, topical steroid preparations or moisturizing creams are commonly applied. Improvement of symptoms of hand-foot syndrome has been reported when vitamin B6 (50–150 mg, twice daily) is taken during continuous infusion of 5-FU 23). When vitamin B6 is administered, the contents of the treatment should be specified in the case report.

As for the presence or absence of the prophylactic administration of vitamin B6 formulation for hand-foot syndrome, both positive and negative reports have been reported 24-30). When used, utilize with application of moisturizing cream prior to the appearance of symptoms.

- Vitamin B6 formulation (60 mg/day) administered daily (continued even during capecitabine withdrawal)
- Frequent application of moisturizing cream (estimate: 5 times or more per day)

[Reference: National Health Insurance approved dose of vitamin B6 preparation]

Pyridoxal phosphate (Pydoxal tablets): 60 mg/2 times/day

Pyridoxine hydrochloride (Aderoxin tablets): 100 mg/day

Pyridoxal hydrochloride calcium powder (Aderoxal powder): 60 mg/3 times/day

2) Supportive care for diarrhea

For diarrhea, loperamide, etc. may be given, and preventive measures after onset can also be taken. In serious cases, appropriate measures such as infusion should be taken.

3) Supportive care for nausea and vomiting

For nausea/vomiting, 5-HT3 formulations such as granisetron hydrochloride and other antiemetic drugs may be used, and preventive measures after onset can also be taken.

4) Combination therapy for neutropenia

In principle, the dosing criteria for G-CSF preparations (such as renograstim) should be as described in the package insert, and prophylactic administration should not be performed. G-CSF preparations may be administered at the discretion of the attending physician in cases in which a decrease in neutrophil count or WBC count of Grade III or higher with fever or a decrease in neutrophil count or WBC count of Grade IV is observed.

5) Combination therapy for fever/infection

If infection accompanied by fever is suspected, antibiotics should be administered. In principle, prophylactic administration of antibiotics is not performed.

## **5-8. Post-treatment**

Post-treatment should not be performed to address underlying illnesses (chemotherapy, endocrine therapy, molecularly targeted therapy, immunotherapy, etc.) until cancerous recurrence is confirmed after termination of the protocol treatment. Post-treatments administered after completion or termination of the protocol treatment and after confirmation of recurrence are not specified.

# **6. Examination/Observation Items**

## **6-1. Pre-Enrollment Examination/Observation Items**

1) Patient background

Sex, age at enrollment, date of written consent acquisition, past medical history, etc.

2) Lesions and evaluation

Histopathological findings of primary lesion (occupied area, tissue type, depth of wall invasion, number of lymph node searches, lymph node metastasis (number, N degree: N1, N2, N3), lymph vascular invasion, presence or absence of venous invasion, date of surgery, presence or absence of preoperative complications, presence or absence of postoperative complications, surgical operation type, observation method (laparotomy, laparoscope), degree of lymph node dissection, etc.

3) Pregnancy test (if applicable)

4) Treatments for comorbidities, complications

5) Electrocardiogram (ECG) * Preoperative examination also counts

6) Chest simple radiographic examination, abdominal ultrasonography or abdominal computed tomography (CT) * Examination can be performed before surgery

7) Vital signs and performance status (PS)

Height, weight, PS

8) Hematological examination (within 14 days before enrollment)

RBC count, hemoglobin, hematocrit, WBC count, leukocyte fraction, platelet count

9) Blood biochemistry testing (within 14 days before enrollment)

Serum total bilirubin, AST, ALT, ALP, total protein, serum creatinine

10) Tumor markers (within 14 days before enrollment)

CEA, CA 19-9

11) Subjective symptoms

